### **Data collection**

As shown in Table 1, prior to the study, uniform training will be delivered by research staff to data collectors. All study data are anonymized and treated confidentially.

Informed consent will be obtained from all ICU nurses prior to study participation. After that, basic demographic data of ICU nurses are collected, including: age, gender, marital status, education background, departments where they worked, years of ICU experience, professional title, baseline CL and level of knowledge. Level of knowledge refers to the nurses' knowledge of ICU delirium assessment tools, risk factors, prevention and intervention acquired through learning, or clinical practice, and measured using the Questionnaire of ICU delirium knowledge. A 20-item multiple-choice knowledge questionnaire was newly developed, with content validity was 0.96, overall cronbach's  $\alpha$  values of the questionnaire was 0.814. The higher of the score, the higher knowledge regarding ICU delirium. During the study, CL and adherence to interventions of ICU nurses are recorded each day at the end of the shift. Data are stored on electronic file powered by a data manager.

**Table 1 ICU nurses' adherence to delirium intervention improvement protocol  
schedule of forms and procedures**

|                            | Assessment time | Recruitment | Baseline   | Daily      | End of the |
|----------------------------|-----------------|-------------|------------|------------|------------|
| Assessment content         |                 |             | assessment | assessment | study      |
| Enrollment          |                 |             |            |            |            |
| Eligibility screen         |                 | ×           |            |            |            |
| Informed consent           |                 | ×           |            |            |            |
| Baseline assessment |                 |             |            |            |            |
| Age                        |                 |             | ×          |            |            |
| Gender                     |                 |             | ×          |            |            |
| Marital status             |                 |             | ×          |            |            |
| Education background       |                 |             | ×          |            |            |

|                                                             |   |   |  |   |
|-------------------------------------------------------------|---|---|--|---|
| Ethnicity                                                   | × |   |  |   |
| Department                                                  | × |   |  |   |
| Years of ICU experience                                     | × |   |  |   |
| Professional Title                                          | × |   |  |   |
| Level of knowledge about ICU delirium                       | × |   |  |   |
| Allocation                                           | × |   |  |   |
| Interventions                                        |   |   |  |   |
| AI-AntiDelirium                               |   | × |  |   |
| Step1: ICU delirium assessment                              |   | × |  |   |
| Step2: Risk factors assessment                              |   | × |  |   |
| Step3: Nursing care plan                                    |   | × |  |   |
| Step4: Nursing Checklist                                    |   | × |  |   |
| Paper-based PADIS guideline                          |   | × |  |   |
| Step1: ICU delirium assessment                              |   | × |  |   |
| Step2: Risk factors assessment                              |   | × |  |   |
| Step3: Nursing care plan                                    |   | × |  |   |
| Step4: Nursing Checklist                                    |   | × |  |   |
| Outcomes                                             |   |   |  |   |
| Adherence to ICU delirium assessment                        |   | × |  | × |
| Adherence to risk factors assessment                        |   | × |  | × |
| Adherence to delirium prevention or management intervention |   | × |  | × |
| Cognitive load                                              | × | × |  | × |
| <hr/>                                                       |   |   |  |   |
| Data management                                      |   |   |  |   |

All data will be collected on a printed, precoded forms that will be double entered into an electronic data base and go through extensive error checking and data completeness. The ICUs involved in the study only have access to their own data. We will perform the following processes to promote data quality: (1) Before the study, all investigators and data collectors will be trained to master the procedures of data collection; (2) All participate nurses will be trained to apply the tools, but different group nurses will attend different education session, intervention group nurses will learn how to use the *AI-AntiDelirium*, control group nurses will learn how to use the PADIS guideline; (3) Data cleaning and reviewing will be utilized incessantly to recognize missing and inconsistencies data. The investigator will solve any problems promptly.

### **Statistical methods**

All data will be analysed using SPSS version 21.0 (SPSS Inc Chicago, Illinois) with an intention-to-treat (ITT) principle, missing data will be imputed using multiple imputations. Statistical analyses will be done by a statistician who is blind to intervention allocations. Continuous variables will be described as means and standard deviation (SD) for normally and medians and interquartile range for abnormally distributed data. Comparisons between groups will performed with the Mann-Whitney U-test (analysis of variance) or Wilcoxon test, including cognitive load, adherence, duration of ICU delirium, length of ICU stay, length of stay in the hospital. Categorical variables will be expressed as frequencies and percentages. Chi-Square test or Fisher's exact test will used to examine between-group differences among incidence of delirium, baseline delirium risk factors and demographics.

Considering the correlation that results from repeated measurements on the same individual, repeated measures analysis of variance (RMANOVA) is used to analyze the multiple measurements variable which is gathered on everyday, such as CL,

adherence of ICU nurses. We will adjust for age, educational level, years of ICU experience, level of knowledge, since these factors were likely to be associated with adherence and CL. Bonferroni post hoc tests were used to assess within-group changes over time, as well as between-group differences during study intervention. Differences in incidence of delirium between groups are analyzed after adjusting for demographic variables using generalized estimation equation. All tests are two-tailed, and P - value < 0.05 is considered statistically significant.

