**Summary**

High cognitive load of nurses is a common problem in intensive care unit, which is associated with nurses' poor performance of activities, as well as related to poor patient outcomes. It remains unclear whether Artificial Intelligence Assisted Prevention and Management for **Delirium** (*AI-AntiDelirium*) results in reduction of cognitive load and enhances adherence to delirium intervention in ICU nurses. We aim to assess the effectiveness of *AI-AntiDelirium* on cognitive load and adherence to delirium interventions of ICU nurses and the impact of ICU delirium. This is a multicentre, prospective, cluster randomised controlled clinical trial comparing the impact of *AI-AntiDelirium* and PADIS guideline for ICU nurses. A total of six ICUs in two hospital will be randomised in a 1:1 ratio to receive either *AI-AntiDelirium* (intervention group) or PADIS guideline (control group), with target sample size of 78 ICU nurses. The primary endpoint will be the adherence to delirium interventions. The secondary endpoints will be the cognitive load which measured by an instrument for measuring different types of cognitive load (MDT-CL). The endpoints of patients included incidence and duration of ICU delirium, length of ICU and in-hospital stay, ICU and in-hospital mortality. Outcome assessments will be conducted by investigators who blind to group assignment. The repeated measures analysis of variance (RMANOVA) will be performed to detect the difference in adherence and cognitive load between groups. Generalized estimation equation will be performed to

test the difference in patient outcomes.

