### **Outcomes**

Endpoint assessment will implement by trained research staffs who will not involve in the clinical nursing care of patients.

**The primary outcome is adherence to the intervention, which** is defined as the adherence of nurses to implement ICU delirium and risk factors assessment, delirium prevention and management interventions every day. The reasons for non-adherence will record daily by the intervention staff.

- a. Adherence to ICU delirium assessment was calculated by dividing the number of actions to number of theoretical assessment. The theoretical ICU delirium assessment for each nurse per day was defined as twice daily multiply the number of patients cared by the nurse.
- b. Adherence to ICU delirium risk factors assessment was calculated by dividing the number of actions to number of theoretical risk factors assessment. The theoretical risk factors assessment for each nurse per day was defined as once daily multiply the number of patients cared by the nurse.
- c. Adherence to ICU delirium prevention or management intervention was calculated by dividing the number of actions to number of theoretical interventions implementation

**Secondary endpoints** will include cognitive load of nurses, **which** defined as the total amount of limited cognitive resources that a person is occupied during a cognitive task. Cognitive load was assessed by means of an instrument for measuring

different types of cognitive load (MDT-CL) with **ten-item**, which had been successfully used to distinguish different types of cognitive load. Each item score from 0 to 10, the higher of the score, the higher of the cognitive load. Cronbach's  $\alpha$  of Chinese version MDT-CL was 0.818, cronbach's  $\alpha$  values in measurement of intrinsic CL (Items 1, 2, and 3) was 0.879; cronbach's  $\alpha$  values in measurement of extraneous CL (Items 4, 5, and 6) was 0.878; cronbach's  $\alpha$  values in measurement of germane CL (Items 7, 8, 9, and 10) was 0.946.

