### **Sample size**

The aim of the cluster RCT is to improve the adherence to delirium intervention of ICU nurses by using the *AI-AntiDelirium* compared to the PADIS guideline. We expect that adherence to delirium intervention in the *AI-Antidelirium* group is 80% and PADIS guideline group is 50%, suggesting that *AI-Antidelirium* has clinical significance in improving the adherence to delirium intervention of ICU nurses. Sample size calculations showed that 12 nurses in each cluster will provide 80% power and a two-sided significance level ( $\alpha$ ) of 0.05, with an intracluster (within-unit) correlation of 0.002. In addition, taking into account possible dropout rate of 10%, we plan to enroll 13 nurses in each ICU, the final sample size is 78 (13\*6) nurses.

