### **Randomisation**

The risk of between-group contamination is reduced by cluster randomisation, ICUs will be randomised 1:1 to receive either *AI-AntiDelirium* care or PADIS guideline. We plan to recruit 6 ICUs in two hospitals, and matching the types of ICU (considering the different types of ICU nursing process, workload and patients illness severity and other factors which will affect the nurses' adherence). The allocation sequence is based on computer-generated random numbers, which is performed by a statistician who is independent of data analyses and not involved in data collection. In order to ensure the allocation concealment, the statistician will inform the each ICUs' allocation code to the study coordinator. And then, the study coordinator will inform the ICU nurses about which group they are allocated. All eligible nurses are recruited until the sample size is enough.

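### ICUs are randomised, but the tests named for adherence and cognitive load treat nurses as independent, so their p-values hold only if the ICU-level correlation is essentially zero

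*Protocol*

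**What the plan says.** Randomisation makes the ICU the unit of allocation: "The risk of between-group contamination is reduced by cluster randomisation, ICUs will be randomised 1:1". It continues: "We plan to recruit 6 ICUs in two hospitals, and matching the types of ICU", because nursing process, workload and illness severity differ by type and affect adherence. Study design and setting lists two surgical, two respiratory and two cardiac ICUs.

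Sample size acknowledges clustering. It plans 12 nurses per ICU for 80% power at 80% against 50% adherence, "with an intracluster (within-unit) correlation of 0.002".

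The analysis text does not carry this through. The Summary says: "The repeated measures analysis of variance (RMANOVA) will be performed to detect the difference in adherence and cognitive load between groups". Statistical methods justifies the choice by the nurse alone: "Considering the correlation that results from repeated measurements on the same individual, repeated measures analysis of variance (RMANOVA) is used to analyze". The adjustment list is age, education, ICU experience and delirium knowledge; ICU, ICU type and hospital are absent. A second route is given as well: "Comparisons between groups will performed with the Mann-Whitney U-test (analysis of variance) or Wilcoxon test, including cognitive load, adherence". Generalised estimating equations appear only for patient outcomes, and the clustering unit is not stated.

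**The concern.** In a cluster-randomised trial the arm difference must be judged against variation between the randomised units. Repeated-measures ANOVA on nurses handles days within a nurse. It then tests the arm effect against variation between nurses, on 78 − 2 = 76 df before covariates and dropout. Rank tests have no error df, but they too assume that nurses are independent. Nothing named for adherence or cognitive load brings in variation between ICUs, where there are only three units per arm.

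If ICUs differ for reasons that the matching does not balance (hospital, local practice, staffing), part of that difference is credited to the intervention and the p-value does not reflect it. The protocol accepts that such variation exists, since it assumes a non-zero ICC and matches on type. Because it names the tests, the correlation they handle and the covariates, this is a stated choice and not a detail left to a statistical analysis plan.

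**Working it through.** **Inputs from the protocol:** 6 ICUs, 3 per arm; 12 evaluable and 13 enrolled nurses per ICU; ICC 0.002; 80% v 50%; two-sided 5%. **Assumptions:** ICCs of 0.05, 0.10 and 0.20, and the share of between-ICU variance that ICU type explains. The protocol gives neither.

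**1. The stated sample size.** Unpooled two-proportion formula: (1.96 + 0.8416)² × (0.16 + 0.25) / 0.30² = 7.849 × 0.41 / 0.09 = 35.76 per arm. The design effect is 1 + 11 × 0.002 = 1.022, so 35.76 × 1.022 = 36.5 per arm, or 12.2 per ICU. This agrees with the stated 12. The sizing therefore allows for clustering, but with normal quantiles.

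**2. Type I error when the ICU is ignored, type explaining nothing.** With m nurses per ICU and ICC ρ, the variance of the arm difference is larger than the test assumes by the factor D = 1 + (m − 1)ρ. The true two-sided error is 2 × [1 − Φ(1.96/√D)].

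**3. The same with matching.** If each type is split across arms and type explains a share s of the between-ICU variance, that share cancels and D = (1 − ρ) + mρ(1 − s).

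Results for m = 13. The simulations used 40,000 null trials per setting and a t-test on nurse means, which equals the between-group test of the repeated-measures ANOVA without covariates.

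| ICC | D, s = 0 | Error, formula | Error, simulated | D, s = 0.5 | Error, formula | Error, simulated |
|---|---|---|---|---|---|---|
| 0.002 (protocol) | 1.024 | 5.3% | 5.3% | 1.011 | 5.1% | – |
| 0.05 (assumed) | 1.60 | 12.1% | 12.3% | 1.275 | 8.3% | about 8% |
| 0.10 (assumed) | 2.20 | 18.6% | 19.2% | 1.55 | 11.5% | about 12% |
| 0.20 (assumed) | 3.40 | 28.8% | 29.9% | 2.10 | 17.6% | about 19% |

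Across runs with 12 or 13 nurses, the error at ICC 0.002 was about 5.1 to 5.4%. If type explains 80% of the between-ICU variance (m = 12), the simulated errors at 0.05, 0.10 and 0.20 are 5.9%, 7.0% and 9.5%.

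**4. ICU-level tests.** Six ICU means less a mean and an arm effect leave 4 df; removing two type contrasts leaves 2 df. If type explains nothing, the unmatched 4-df t-test on ICU means holds about 5% at every ICC. If types are split and explain half, it rejects only about 2.6 to 3.7% at ICCs of 0.05 to 0.20. The paired 2-df test stays near 5%.

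**5. Power at ICU level.** With 12 nurses per ICU and ICC 0.002, the standard error is √(0.41/36 × 1.022) = 0.108 and the noncentrality is 0.30/0.108 = 2.78. Critical t is 2.78 on 4 df and 4.30 on 2 df, against 1.99 on about 70 df. Noncentral-t power is about 56% on 4 df, and about 35% on 2 df before any gain from matching. On 4 df it is about 41% at ICC 0.05 and 32% at 0.10.

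**The case against.** The best defence is that 0.002 is the only ICC in the document and the inflation there is trivial. That is true, and it is why the point cannot be put as a demonstrated large excess of false positives. It does not rescue the analysis. The protocol takes 0.002 from a cited trial whose title concerns fall prevention in acute care hospitals and gives no ICC for nurse adherence. The arm test also works on each nurse's average over days. If 0.002 describes a single day, averaging removes daily noise but not ICU variance. For example, with 30 days and an assumed 10% of variance between nurses, the ICC of the average is 0.002 / (0.002 + 0.1 + 0.898/30) = 0.015, and the error is about 7% (m = 12).

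The matching is the second defence, and it stands in part. A reader might infer that 12%, 19% and 30% are the expected error rates, or that every ICU-level difference passes for an intervention effect. Neither follows. Those figures are upper values for the assumed ICCs, reached when type explains nothing. If each type is split across arms, differences between types balance, and only hospital or ICU differences within a type carry over. The protocol does not say outright that each type is split; if it is not, the upper values apply.

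A reader might also infer that a planned confidence interval is too narrow by a fixed factor. The protocol mentions no confidence intervals, so no such interval can be measured. Finally, Statistical methods never labels the repeated-measures ANOVA the primary analysis. The Summary and Statistical methods do name it for the primary outcome, and the rank tests also listed share the fault.

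**Conclusion.** The point holds. The analyses named for adherence and cognitive load ignore the randomised unit, contradicting the protocol's own design and sample-size basis, and nothing else in the document repairs this. Their between-arm p-values are valid only if the ICC is essentially zero.

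The size depends on an ICC that the documents do not establish for adherence. The inflation is negligible at 0.002 and becomes material at the assumed values of 0.05 and above, by an amount that depends on how much ICU type explains. A flat statement that the false-positive rate is well above 5% goes further than the documents allow. A second consequence does not depend on a larger ICC: an ICU-level test with six ICUs does not give the stated 80% power, even at 0.002.

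**What to change.** - Replace the nurse-level between-arm tests of adherence and cognitive load, including Mann-Whitney and Wilcoxon. Use either a mixed model with random effects for ICU and for nurse within ICU and small-sample df (Satterthwaite or Kenward-Roger), or a two-stage comparison of covariate-adjusted ICU means.
- State in advance whether the ICU-type matching is kept (2 df, error near 5%) or ignored (4 df, valid but conservative if matching is effective), and whether each type is split across arms.
- Report the estimated ICC for adherence and for cognitive load.
- Do not rely on two apparent shortcuts. Sandwich standard errors on six clusters are themselves anti-conservative without a small-sample correction. An exact permutation test on three pairs has 2³ = 8 allocations and cannot go below a two-sided p of 2/8 = 0.25.
- Restate the power in Sample size.

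No new data are needed, but the change is more than wording. For 80% against 50% with 12 nurses per ICU and ICC 0.002, power is about 56% on 4 df, or about 35% on 2 df before any gain from matching. That limit comes from having six ICUs, and the nurse-level analysis hides it. The change should be made before unblinded analysis.

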## **Background**

Cognitive load refers to the total amount of cognitive resources that a person needs to process cognitive activities, and is composed of three different types: intrinsic CL, extraneous CL and germane CL. Higher CL, which exceeds one's working memory resource capacity, has been identified as one of the most important problems in providing intensive care. It negatively impacts nurses and their patients, which can lead to irritability, memory impairments and mental fatigue of nurses, is detrimental to performance of activities, reduced learning capacity for acquiring knowledge, and also results in poor patient outcomes and compromises patient safety. The more complicated are the activities performed by nurses, the higher the CL are required, which will hinder the adherence to implement nursing activities.

Nursing care in intensive care units (ICU) is characterized by extremely demanding caseloads, performance of complicated activities and making complex decisions. One example is the complex care required in ICU delirium prevention and management interventions. ICU delirium is a common complication of ICU patients with an high incidence of 70% to 87%, and associated with longer hospital length of stay (LOS) and increased mortality. Therefore, the Clinical Practice Guidelines for the Prevention and Management of Pain, Agitation/Sedation, Delirium, Immobility, and Sleep Disruption in Adult Patients in the ICU (PADIS guideline) recommend use of the ABCDEF bundle as a way to prevent and manage ICU delirium, which focuses on eliminating ICU delirium risk factors. However, adherence to the ABCDEF bundle is sub-optimal in routine clinical care. Previous studies have demonstrated that various barriers may hinder the adherence to

implement the bundle, such as heavy workload on nursing care records, complexity algorithm of assessment tools, struggle to collect and remember numerous risk factors through multiple channels, lack of knowledge about ICU delirium^27. Working on complicated activities results in lowered speed for receiving and processing information, decreased capacity of working memory and requires higher cognitive load (CL).

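### Baseline cognitive load is collected from every nurse but left out of the covariates for the secondary cognitive-load analysis, giving up precision and some protection against chance imbalance

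*Protocol*

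**What the plan says.** All references are to the Protocol.

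- **Collection.** The Data collection section lists, among the items recorded after consent, "professional title, baseline CL and level of knowledge". The Table 1 row "Cognitive load" agrees: it carries one more mark than the adherence rows, in an earlier column.
- **Follow-up.** In the same section, "CL and adherence to interventions of ICU nurses are recorded each day at the end of the shift".
- **Model.** Under Statistical methods, "repeated measures analysis of variance (RMANOVA) is used to analyze the multiple measurements variable which is gathered on everyday, such as CL" and adherence.
- **Covariates.** The same section continues: "We will adjust for age, educational level, years of ICU experience, level of knowledge, since these factors were likely to be associated with" both of these outcomes. That is a closed list of four, with the reason for choosing them.
- **Other uses of baseline CL.** None is stated. The Mann-Whitney or Wilcoxon comparison of CL is unadjusted, and the Bonferroni comparisons are not said to use baseline.
- **Allocation.** Under Randomisation, "ICUs will be randomised 1:1 to receive either" the AI tool or the PADIS guideline. With six ICUs that is three per arm, matched on ICU type.

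**The concern.** The protocol states a rule for choosing covariates, namely likely association with the outcomes, and then omits the collected variable that fits the rule most directly for CL: the nurse's own starting value on the same instrument. Level of knowledge, named beside baseline CL in the data collection list, is included. Because the list is explicit, this is a choice already made and not a detail left open.

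Two things are at stake for the CL comparison. One is precision: variation between nurses that baseline CL would explain stays in the error term. The other is imbalance: with three ICUs per arm, the arms may start with different mean CL, and an analysis that ignores baseline carries part of that difference into the estimated effect.

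**Working it through.** **The plan's own figure.** The sample size rests on adherence of 80% versus 50%, two-sided 0.05, 80% power, ICC 0.002 and 12 nurses per ICU.

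- Unpooled two-proportion formula: (1.960 + 0.842)² × (0.80×0.20 + 0.50×0.50) / 0.30² = 35.76 per arm.
- Design effect: 1 + (12 − 1) × 0.002 = 1.022.
- Required: 35.76 × 1.022 = 36.5 per arm, or 12.2 per ICU. The stated 12 is reproduced; power at 12 is 79.4%.
- Dropout: 12/0.9 = 13.3, taken as 13, giving 13 × 6 = 78.

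This calculation concerns adherence and assumes no covariate adjustment, so the omission changes none of it.

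**Inputs for the CL question.**

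- From the protocol: six ICUs, three per arm; 12 nurses per ICU analysed, 13 enrolled (39 per arm); ICC 0.002. The protocol gives this ICC for adherence; applying it to CL is an assumption.
- Not in the protocol, so assumed: correlation r between baseline and follow-up CL of 0.3, 0.5 or 0.7; an alternative ICC of 0.10.

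**Step 1: nurse-level variance, single follow-up value.** Adjustment multiplies residual variance by 1 − r².

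| r | 1 − r² | Reduction |
|---|---|---|
| 0.3 | 0.91 | 9% |
| 0.5 | 0.75 | 25% |
| 0.7 | 0.51 | 51% |

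**Step 2: daily measurement.** CL is recorded repeatedly, so a single value is a simplification. For the mean of k days under compound symmetry, the unadjusted variance is (1 + (k − 1)r)/k, and adjustment subtracts r². With k = 5 (assumed):

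- r = 0.3: (0.44 − 0.09)/0.44 = 0.80
- r = 0.5: (0.60 − 0.25)/0.60 = 0.58
- r = 0.7: (0.76 − 0.49)/0.76 = 0.36

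Averaging over days therefore makes the nurse-level gain larger. The four covariates already listed could make it smaller, by an amount the protocol does not allow one to compute.

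**Step 3: the arm contrast.** Suppose adjustment reduces only the nurse-level part. In units of total variance, an ICU mean of 12 nurses has variance ICC + (1 − ICC)/12. With r = 0.5:

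- ICC 0.10: before, 0.10 + 0.90/12 = 0.175; after, 0.10 + 0.75 × 0.90/12 = 0.156. Reduction about 11%.
- ICC 0.002: before, 0.002 + 0.998/12 = 0.0852; after, 0.002 + 0.75 × 0.998/12 = 0.0644. Reduction about 24%.

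**Step 4: chance imbalance.** The difference between arms in mean baseline CL, in nurse-level SD units, has SD √(2 × (1 + 12 × ICC)/39).

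- ICC 0.002: √(2 × 1.024/39) = 0.23; chance of a difference above 0.3 SD either way, about 19%.
- ICC 0.10: √(2 × 2.2/39) = 0.34; chance about 37%.

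Neither figure credits the matching on ICU type. An imbalance of 0.3 SD with r = 0.5 would shift an estimate that ignores baseline by about 0.3 × 0.5 = 0.15 SD.

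**The case against.** **It affects a secondary endpoint only.** This stands. Table 1 shows no baseline adherence, and the trial was sized on adherence. The Background does say of CL that "the higher the CL are required, which will hinder the adherence to implement nursing activities", so a reader might infer that the primary analysis is also deficient. But the protocol gives no figure for the association of baseline CL with adherence, so a gain there cannot be claimed.

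**Imbalance is not likely in the ordinary sense.** This stands too. The chance of exceeding 0.3 SD is 19% or 37%, and matching on ICU type, chosen because type bears on workload and illness severity, should lower it. Matching does not balance individual nurses, or the two hospitals' ICUs of one type.

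**The size is assumed.** Correct: no correlation is given, and Step 1 matches neither the daily design nor a model that already has four covariates. It would be tempting to read r = 0.7 as nearly doubling the sample (1/0.51 = 1.96). That is the favourable end of an assumed range, refers to nurse-level variance only, and supplies no additional ICUs.

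**Baseline may enter as the first time point.** A reader might infer this and conclude that the group main effect is diluted by k/(k + 1), for instance to 5/6 = 0.83 with five daily values. The text does not support it: the analysis is applied to what is gathered daily, and the Bonferroni between-group comparisons refer to the intervention period. If baseline were a time point, a group-by-time contrast would escape that dilution.

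**The covariate is not a complete remedy.** Agreed. A nurse-level slope need not remove a between-ICU difference, since slopes within and between ICUs can differ. CL is self-reported by unblinded nurses, and the text does not say that baseline CL is taken before the coordinator tells them their group. The benefit depends on that order.

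**A later analysis plan could add it.** It could, but the protocol has already stated a list and a criterion, and the two do not agree for CL.

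**Conclusion.** The point holds for the secondary CL endpoint and no further. The protocol collects a baseline value that satisfies its own criterion for adjustment and leaves it out of a closed covariate list. A reader might infer that the CL result would be biased or the comparison invalid. Neither follows: randomisation keeps the estimate unbiased in expectation, and what is given up is precision and some protection against an unlucky draw of six ICUs.

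The nurse-level loss is 9% to 51% of residual variance for a single follow-up value over the assumed correlations. At r = 0.5, the arm contrast loses between about 24% (ICC 0.002) and 11% (ICC 0.10). All these figures depend on assumptions that the protocol cannot confirm. This is a moderate improvement that is nearly free to make.

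**What to change.** In Statistical methods, state that the CL model also includes the nurse's baseline score on the matching MDT-CL scale (the same total or subscale as the outcome), and that only post-baseline shifts are outcomes. In Data collection, state that baseline CL is measured before the nurse is told the ICU's allocation.

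The cost is one degree of freedom in the CL model and a sentence or two of text; the data are already being collected. The primary adherence analysis and the sample size are unchanged. The change does not replace accounting for clustering by ICU, which the description of the repeated measures analysis does not mention and which needs its own provision.
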